### Frequency and plans for auditing trial conduct

Regular monitoring will be performed by the Study Coordinator to evaluate compliance with the protocol. Monitoring will verify that the study is conducted, and data are generated, documented and reported in compliance with the protocol and the applicable regulatory and national policy requirements [70]. Any data issues will be addressed by raising data queries for GP sites to resolve where possible, following this on-site monitoring will be undertaken. Direct access will be granted to authorised representatives from the Sponsor, host institution and the regulatory authorities to permit trial-related monitoring, audits and inspections - in line with participant consent.

### Plans for communicating important protocol amendments to relevant parties (e.g. trial participants, ethical committees)

Any substantial amendments to the protocol or other study documents may require review and approval by the Research Ethics Committee (REC) before the changes can be implemented to the study. Where amendments are required, NHS HRA and REC procedures will be followed, i.e. any amendment will be shared directly via email with participating sites. Sites will be asked to confirm receipt of the amended documents.

## Discussion

Systematic isometric wall squat exercise, which employs the large muscle mass of the quadriceps, has been shown to be an effective means of lowering resting BP. In a recent relatively small-scale study, Taylor et al. [10] showed that the magnitude of BP reduction following 4 weeks of isometric wall squat exercise in unmedicated high normal participants was greater than when the same intervention was completed by those with BP in the normal range [9]. It was postulated that this IE intervention may exert a greater antihypertensive effect in patients with more severe hypertension such as those diagnosed with stage 1 hypertension. The clinically significant BP reduction observed was also greater than the average BP reduction achieved with a single, standard dose anti-hypertensive drug [71] and is associated with reduced cardiovascular mortality [5]. However, before the efficacy of this novel intervention to treat stage 1 hypertension can be investigated in any large-scale randomised controlled trial, it is first necessary to ascertain if it can be delivered and carried out as intended in (as ultimately envisioned) an NHS primary care setting. If it can, and patient adherence is found to be equal or better than that documented for other forms of lifestyle invention and resting BP is shown to either decrease or stay the same following the IE intervention, then the findings of this feasibility study will support the viability of IE as both a prophylactic and alternative treatment option for thousands of NHS patients wishing to avoid antihypertensive drug therapy. Importantly, the results of this study will determine uncertain parameters needed to design a substantive efficacy study, including the variance in BP change needed for sample size calculation, the ability to deliver the intervention as intended in primary care, recruitment rates, and participant acceptability and compliance. Moreover, the economic analysis in this feasibility study will determine the acceptability of resource use and utility measures in this setting, establish the cost of the IE intervention programme and conduct some preliminary modelling to explore potential cost effectiveness, prior to a full economic evaluation of the IE intervention programme in the planned definitive trial. The follow-on study will be a randomised, controlled efficacy study pending additional funding. This study will determine uncertain parameters needed to design a substantive trial; variance of the primary outcome measure needed for sample size calculation, ability to deliver the intervention as intended in primary care, recruitment rates and participant acceptability and compliance.

Whilst the advent of Covid-19 has presented a significant challenge, primarily in terms of reliably delivering and evaluating a novel exercise training intervention remotely, it has also provided a valuable opportunity to evaluate alternate methodological approaches/new protocols that may not otherwise have occurred, e.g. the feasibility of using observed patient home BP readings for remote monitoring as opposed to clinic measurements. Since the current pandemic shows little sign of abating, this additional information might help to inform the research design of similar studies planned for delivery during these exceptional times.

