#### Lifestyle interventions

The importance of lifestyle changes to aspects, such as diet and exercise habits for patients with hypertension in the absence of other risk factors should not be overlooked [1, 20]. Additional treatment options are also in keeping with the UK government’s commitment to provide greater patient choice [21]. Whilst dietary strategies can be effective, these are difficult to fully adopt and maintain [22, 23].

Evidence suggests that exercise may be as effective as medication in controlling BP [24–26] and it is often promoted as a treatment option for those with stage 1 hypertension (defined as a blood pressure of 140–159/90–99 mmHg), without co-morbidity or other long-term conditions [1, 27]. Current exercise guidelines for the prevention and treatment of hypertension recommend that adults accumulate a mainstay of 30+ min of moderate intensity aerobic exercise on 5, but preferably all, days per week (d/wk), supplemented by moderate to vigorous resistance exercise 2–3 d/wk and general flexibility exercise ≥ 2–3 d/wk [28, 29]. However, in a randomised controlled trial, a long-term programme of aerobic exercise training failed to reduce clinic BP [30]. This may be due to poor adherence (e.g. 67%) to the relatively high amounts of aerobic exercise recommended [30, 31]. Furthermore, other studies have demonstrated attrition rates as high as 50% during traditional aerobic exercise interventions [32, 33]. Indeed, evidence typically suggests that a significant challenge is the low adoption and high attrition rates associated with these guidelines [34]. Thus, effective and manageable lifestyle interventions with respect to exercise remain an unmet clinical need [3]. It is suggested that to promote lifestyle exercise changes, patients need easily adopted, effective and manageable exercise interventions as a first line option for managing their BP.

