### Sample size

Review of current literature revealed few IE studies in a hypertensive population. These studies were small (*n* < 25), conducted under different conditions to the proposed study, and showed low precision and large variability in estimates of the standard deviation (SD). A sample size of 100 participants, 50 per arm, will be used in the study. Allowing for 20% attrition and 6.5% incomplete data, 74 participants (37 in each arm) will have completed change measures at 4 weeks. This is in line with the recommended sample size of 70 to estimate key parameters from external pilot RCTs [62]. A sample size of 74 produces a two-sided 95% confidence interval with a width of 1.33 when the standard deviation is 4. This estimate of 4 has been taken from a previous study (*N* = 24) [10]. The sample size confidence interval has been calculated using Pass11 software (PASS 11. NCSS, LLC. Kaysville, UT, USA, www.ncss.com).

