Accuracy of IE protocol delivery will be determined using data from three fidelity assessments; the first being healthcare professional competency checks administered during their isometric exercise prescription training; the second being expert observation/evaluation of at least the first IIET delivered by each HCP; and then finally, by third party examination of the first week of heart rate data recorded in the study diaries of each HCP’s specific participants, with average HR calculated from the first 3 sessions being compared against the individuals target training HR as described above.

Execution of the IE training protocol in the home will be assessed for each individual participant at the end of the first week by checking to see if their mean training heart rate per week falls within target heart rate range/reference interval (76–111%) *data for weeks 4, 12 and 24 will now be assessed at the end of the 6-month training period*. An estimate of the short- (4 week) and medium-term (3 and 6 month) adherence rates to IE training will be based upon the data collected from participant diaries to calculate the proportion of participants completing ≥ two thirds of all IE sessions (12, 36 and 72) at each time point respectively. Patient recruitment and participant attrition rates will be calculated based upon the average number of participants recruited per week over the 7 month recruitment period and the number of withdrawals from the study once the last follow-up call to the last participant has been made.

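### The Discussion's viability statement uses an uncontrolled blood-pressure condition, so meeting it cannot separate an active exercise programme from an inert one

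*Protocol article*

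**What the plan says.** The relevant sentence in the Discussion joins three conditions with 'and':

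- delivery: that "it can be delivered and carried out as intended" in NHS primary care;
- adherence: that "patient adherence is found to be equal or better than that documented for other forms of lifestyle invention";
- BP: that "resting BP is shown to either decrease or stay the same following the IE intervention".

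If all three hold, "then the findings of this feasibility study will support the viability of IE as both a prophylactic and alternative treatment option". The Discussion part of the Abstract makes the same claim more cautiously, with 'could'.

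Elsewhere the article plans something different for BP. The primary outcomes (Outcomes, Primary) include the treatment difference in systolic change from baseline with 80% and 95% confidence intervals, as a preliminary assessment of benefit and an aid to deciding on a confirmatory trial. The data-collection section repeats that estimate. Quantitative data analysis specifies ANCOVA adjusted for baseline, centre, sex and age. The viability sentence does not refer to this estimate.

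**The concern.** The trial is randomised, yet the one BP condition tied to the viability claim looks only at the exercise arm. It sets no margin, does not define what counts as unchanged, and counts a zero effect as support.

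The article gives reasons why BP in the exercise arm could move without any effect of the exercise:

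- Both arms receive lifestyle advice (Intervention description), and the leaflet text says that reducing salt lowers BP.
- Participants are selected for raised BP, and those with averaged home systolic BP below 135 mmHg are excluded, so regression to the mean is plausible.
- Change is taken from an observed day-1 baseline to home diary readings. That change of measurement setting could shift the mean in either direction.

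A between-arm contrast removes whatever part of this is common to both arms. A within-arm condition credits it to the exercise. At stake is what may be concluded: a trial with no difference between arms could be reported as supporting exercise for patients who want to avoid medication.

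**Working it through.** **Inputs from the document.** Under Sample size: "74 participants (37 in each arm) will have completed change measures at 4 weeks", and an SD of 4 mmHg. Allocation is 1:1.

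**Assumptions.** SDs of 6, 8 and 10, a common background fall of 1 to 3 mmHg, a true benefit of 5 mmHg and a minimum clinically important difference (MCID) of 5 mmHg are illustrative. The article gives no MCID. It mentions 5 mmHg systolic only as a population reduction, and 12 mmHg as the systolic fall seen in pre-hypertensives.

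**The plan's own figure.** "A sample size of 74 produces a two-sided 95% confidence interval with a width of 1.33 when the standard deviation is 4". The 95% interval for a standard deviation is SD × √((n−1)/χ²). With n = 74 and SD = 4 it runs from 3.443 to 4.773, a width of 1.330, so the figure reproduces. It is the precision of the SD, not of a mean change; the corresponding t interval for one mean has width 1.85. The figure therefore says nothing about how precisely the BP condition can be judged.

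**Inert programme, no background change, n = 37.**

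- Mean change must be at or below zero: 50% at any SD.
- Mean not significantly raised, 80% interval: 1 − 0.10 = 90%.
- Mean not significantly raised, 95% interval: 1 − 0.025 = 97.5%.

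**Inert programme with an assumed common fall δ.** P(mean change ≤ 0) = Φ(δ / (SD/√37)).

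| SD | SE = SD/√37 | δ = 1 mmHg | δ = 2 mmHg |
|---|---|---|---|
| 4 | 0.658 | Φ(1.52) = 93.6% | Φ(3.04) = 99.9% |
| 8 | 1.315 | Φ(0.76) = 77.6% | Φ(1.52) = 93.6% |
| 10 | 1.644 | Φ(0.61) = 72.9% | Φ(1.22) = 88.8% |

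The δ = 1 column also covers a harmful case. A programme that raises BP by 2 mmHg against a background fall of 3 mmHg has a net change of −1, so it passes in 93.6%, 77.6% and 72.9% of trials at SD 4, 8 and 10.

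**Between-arm condition for comparison.** SE = SD × √(2/37), which is 0.930 at SD 4. The 80% half-width is t(0.90, 72 df) × SE = 1.293 × 0.930 = 1.20 mmHg. If the 80% interval must lie below 0, an inert programme passes in 10% of trials, whatever drift the arms share. From the noncentral t, a true 5 mmHg benefit passes in over 99.9%, 98.9%, 91.8% and 80.4% at SD 4, 6, 8 and 10. These figures ignore any gain from covariate adjustment.

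**Adding an MCID condition (assumed 5 mmHg).** Two wordings behave very differently.

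- If the interval must contain the MCID, a clearly better programme fails: at a true 12 mmHg it passes in under 5% of trials at every SD tried, because the interval lies wholly beyond 5.
- If the interval must reach at least the MCID, both conditions together pass in about 90%, 90%, 89% and 80% at a true 5 mmHg (SD 4, 6, 8, 10). At a true 12 mmHg and SD 10, SE is 2.325 and the half-width 3.01, so the pass probability is about Φ((12 − 3.01)/2.325) = Φ(3.87), above 99.9%. The MCID part is then met automatically, since an interval with its upper limit below 0 extends below −6.

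**The case against.** The strongest defence is that this is an interpretive remark in a Discussion, not an analysis rule. That is largely right, and it limits the point in four ways.

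- A reader might take the BP clause as the trial's success rule. It is one of three joined conditions, and Outcomes separately names the between-arm estimate as an aid to the decision on a confirmatory trial. The two texts concern different decisions (viability, and whether to go on to a trial), so they need reconciling rather than being in outright contradiction. The Discussion also says that efficacy still has to be tested in a large trial.
- A reader might infer that an inert programme passes almost always. The documents do not fix that: the plainest reading with no drift gives 50%, and the highest figures need a drift that the article does not quantify. Because screening uses averaged home readings taken before the day-1 baseline, part of any regression to the mean may already have occurred by then.
- A reader might set the 67% that the background calls poor adherence against the two-thirds cut-off used here, which gives "the proportion of participants completing ≥ two thirds of all IE sessions (12, 36 and 72) at each time point respectively". The article does not give the metric behind the 67%, and a study's adherence rate is not the same quantity as a per-person cut-off. No inconsistency can be shown.
- No outcome, sample size or planned analysis depends on the sentence.

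What survives is that the sentence says in advance which results will support viability as an alternative to drug therapy, and its BP part ignores the control arm. The delivery and adherence conditions do not repair this, since a well-delivered, well-followed programme can still have no effect on BP.

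**Conclusion.** The point holds as a flaw in what the article says the trial may conclude, not in its design or analysis. None of the three viability conditions can distinguish an active programme from an inert one. The chance that an inert programme meets the BP condition runs from 50% to nearly 100%, depending on how an unchanged BP is read and on any background fall. These figures rest on 37 completers in the exercise arm and approximate normality of the mean; those with drift also rest on the assumed falls and, above SD 4, on assumed SDs. The 50%, 90% and 97.5% figures do not depend on the SD.

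**What to change.** Reword the Discussion sentence, and align the Abstract, so that the BP condition rests on the adjusted between-arm difference in systolic change with the 80% and 95% intervals already planned. One workable form: *if the exercise can be delivered, adherence is adequate and the 80% confidence interval for the adjusted difference (exercise minus control) lies below 0, the findings will support proceeding to a definitive trial.* Name the time point. Drop the statement that the findings would support viability as a preventive or alternative treatment.

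If an MCID condition is added, give the MCID a value and require the 80% interval to reach at least that value, so that larger effects also pass.

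The change needs no new data or analysis. Its cost is a less favourable claim, and a real but modest benefit could miss the condition if the SD is well above 4: about 20% of the time for a true 5 mmHg at SD 10.

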## Data Availability

Anonymised data will be made available upon request, to researchers at universities, NHS organisations or other healthcare providers where the sharing of data has a clear defined purpose and its use will be of benefit to wider society.

## Abbreviations

BP: Blood pressure
IE: Isometric exercise
NHS: National Health Service
PHE: Public Health England
CKD-EPI: Chronic Kidney Disease Epidemiology Collaboration
MDRD: Modification of Diet in Renal Disease
QALYs: Quality-adjusted life years
AE: Adverse event
SAE: Serious adverse event
CCCU: Canterbury Christ Church University
UKC: University of Kent
EKHUFT: East Kent Hospitals University Foundation Trust
SSC: Study Steering Committee
PMG: Project Management Group
